### Intervention

#### WHBDIP Development

WHBDIP is a web-based individual telehealth intervention program for patients with hypertension on WeChat, which includes nondrug intervention health education and behavior change strategies. WHBDIP consists of 4 sections: exercise, diet, BP monitoring, and medication adherence behavior interventions, which together constitute a comprehensive health behavior intervention program.

The exercise intervention was based on an intelligent personalized exercise prescription. This prescription has been verified by experts and has been proved by a 1-year real-world clinical research [32]. Before prescribing, health data are collected by an intelligent health promotion system (including networked equipment and a questionnaire system) installed in the community health service center. The intelligent decision-making module of this system generates safe, reliable, and personalized prescriptions according to the complex health conditions of the residents, especially older patients with 1 or more chronic diseases. In WHBDIP, the health education content matching the exercise prescription was compiled into text and then transformed into animation or video to be included in the electronic knowledge base.

The dietary intervention was designed based on the principles of the DASH. After revising the simplified DASH grading diet index score (SDGDIS), videos related to DASH health education were produced and delivered to subjects through WeChat. Subjects were required to upload photos of their 3 meals per day (including a fist for size comparison) within 7 days. The scores (based on the SDGDIS) and qualitative evaluation text were provided to subjects during this period. After 7 days, the subjects and interveners were required to provide their respective scores.

For BP monitoring and medicine adherence (MA) intervention, we have created health education videos and used WeChat to send reminders and supervise the health behavior of the subjects. The content of health education related to WHBDIP is displayed in Table 1, and the video screenshots are shown in Figure 1.

**Figure 1 figure1:**
[figure not shown]
Video screenshots.

**Table 1 table1:** Topics and forms of health education content.

Topic		Form
**Exercise intervention**		
	Intelligent personalized exercise prescription	Pictures and text
	The benefits of exercise	Video
	The difference between aerobic and anaerobic exercise	Video
	The choice of exercise intensity	Pictures and text
	Seated strength training for the older	Video
	Running breath	Video
	Running posture	Video
	When should stop exercising	Video
	Aerobics for middle-aged and older	Video
	Stretching	Video
**Dietary intervention**		
	What is the “DASH”^a^	Video
	“DASH” teaches you how to eat	Video
	How to rate your “DASH”?	Video
**BP^b^ monitoring**		
	How to choose a sphygmomanometer	Video
	How often should BP be measured?	Video
	How much does BP drop to reach the target?	Video
	The use of mercury sphygmomanometer	Video
	The use of upper arm electronic sphygmomanometer	Video
	The use of wrist electronic sphygmomanometer	Video
**MA^c^ intervention**		
	Why can't stop taking the medicine on my own?	Video

^a^DASH: Dietary Approaches to Stop Hypertension.

^b^BP: Blood pressure.

^c^MA: Medicine adherence.

To promote adherence behavior change, we adopted the behavior change wheel (BCW), which is a systematic framework for selecting 25 behavior change techniques (BCTs) from Michie et al's [33] taxonomy that correspond to the 9 intervention functions (shown in Table 2). The use of BCTs was documented in the intervention manual.

**Table 2 table2:** Implementation of BCTs^a^ following Michie et al’s [33] BCW^b^ and taxonomy.

Intervention functions and BCTs		Examples
**Education: increasing** **knowledge or understanding**		
	4.1 Instruction on how to perform the behavior	Provide healthy educational content on how to exercise and eat
	5.1 Information about health consequences	Tell the intervention the benefits of exercising
	4.3 Reattribution	If the subjects attributed their lack of exercise to frequent bad weather, intervenor indicated that the “real” reason might be the person's lack of motivation
**Persuasion: using** **communication to induce positive or negative feelings or stimulate action**		
	15.3 Focus on past success: advise to think about or list previous successes in performing the behavior	Suggest the subjects to think about or list the successful experience of a certain behavior (quit smoking and drinking) before to convince him that he can also develop the habit of scientific exercise or diet
	15.1 Verbal persuasion about capability	Tell the subjects that they can successfully increase their physical activity
	13.5 Identity associated with changed behavior	Ask the subjects to articulate their new identity as “ex-inactive person”
**Incentivization: creating** **an expectation of reward**		
	10.2 Material reward (behavior)	Arrange for the subjects to receive WeChat red packet (money)
	10.6 Nonspecific incentive	Indicates a happy mood for completing the task, such as instructing the subjects to imagine that he has successfully completed today's exercise task, sweating profusely, and feeling happy
Coercion: creating an expectation of punishment or cost		
	—^c^	—
**Training: imparting** **skills**		
	8.1 Behavioral practice or rehearsal	Ask subjects to continue to rate their diet for 7 days
	15.4 Self-talk	Encourage the subjects to use talk to themselves (aloud or silently) before and during exercise to encourage, support and maintain action, like “I Can!”
Restriction: using rules to reduce the opportunity to engage in the target behavior (or to increase the target behavior by reducing the opportunity to engage in competing behaviors)		
	—	—
**Environmental restructuring: changing the physical or social context**		
	12.6 Body changes	Remind the subjects to stretch before and after exercise (except health care type) to prepare their bodies
	12.2 Restructuring the social environment	Encourage the subject to invite family members or friends to exercise together
	3.1 Social support	
Modeling: providing an example for people to aspire to or imitate		
	—	—
**Enablement: increasing** **means or reducing barriers to increase capability (beyond education and training) or opportunity (beyond environmental restructuring)**		
	1.1. Goal setting (behavior)	Determine the weekly exercise time based on exercise prescriptions
	2.7 Feedback on outcomes of behavior	Feedback on diet score and comprehensive evaluation
	2.4 Self-monitoring of behavior	Provides a subjective method to assess exercise intensity and allows subjects to self-monitor
	1.9 Commitment	Sign a contract with subjects that they can do healthy behavior
	1.4 Action planning	Prompt planning of a particular physical activity (running) at a particular time (before work) on certain days of the week
	1.5 Review behavior goals	Examine how well subjects’ performance corresponds to agreed goals such as exercise 30 minutes at a time
	1.6 Discrepancy between current behavior and goal	Compare the difference between the real exercise volume and the target volume
	7.1 Prompts or cues	Send medication reminder to subject
	8.3 Habit formation	Ask the subjects to check in on sports and upload photos of their diets every day
	7.3 Reduce prompts or cues	Reduce medication reminders
	1.2 Barrier identification or problem solving	Analyze the reasons (information are collected by questionnaire) for impeding movement and provide solutions (according to intervention manual)
	4.2 Information about antecedents: advise to keep a record of situations or events occurring prior not to exercise	Record the reasons for not exercising
	11.2 Reduce negative emotions	Instruct the subject to perform relaxation exercises in situations when exercise brings about negative emotions

^a^BCTs: behavior change techniques.

^b^BCW: behavior change wheel.

^c^Not available.

#### Validation of WHBDIP

The WHBDIP (health education content and intervention plan) has been validated through a 2-round Delphi survey by a panel of experts. The panelists consisted of 15 experts, including 4 nutritionists and 1 professor of nutriology, 2 clinical cardiologists, 3 clinical nurses or nursing teachers, and 5 exercise-related experts. All of them held a bachelor’s degree or higher and had at least 5 years of work experience in their respective fields. The panelists were divided into 3 groups to evaluate the content’s appropriateness and relevance for exercise, diet, and BP monitoring or MA management. The content validity index (CVI) was calculated using item-level content validity index (ICVI) and rated on a 4-level scale. In the first round, the ICVI ranged from 0.6 to 0.8. Based on the experts' comments, the content was modified. In the second round, the ICVI reached 1.

### Intervention Procedure and Monitoring

Prior to the experiment, we conducted a physical examination on the subjects at the intelligent health hut and used the system to generate intelligent exercise prescriptions. Health behavioral digital intervention was provided to the experimental group by 5 trained interventionists through WeChat. The interventionists sent health education materials, specific text (such as reminders to take medicine or exercise), or electronic questionnaires according to the intervention manual's procedures. They collected data or pictures about exercise, diet, self-measured BP, and medication every day during the initial 3 months. The control group received routine health interventions, including oral health education about printed exercise prescriptions, dietary guidance, BP monitoring, and the importance of regular medication. After the program, they will have free access to health education electronic materials.

### Randomization, Allocation, and Blinding

This study followed a process of randomization. Before randomization, an individual not involved in subject recruitment and data collection used the SPSS software (version 23; IBM Corp) to generate 68 random numbers and assigned them to either 1 (experimental group) or 2 (control group) using visual binning. These 68 sets of random numbers were printed separately and sealed in individual envelopes. After recruiting a participant, the facilitator opened the envelopes sequentially, and the number found inside each envelope determined the group to which the particular participant belonged. In this study, we blinded data collectors both before and after the trial.

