## Methods

### Trial Design and Setting

This is a 2-arm, parallel-group, randomized trial that includes a WeChat-based health behavioral digital intervention lasting for 12 weeks. The trial has been conducted at 2 community health centers, both located in Anhui province—1 in Hefei and the other in Bengbu. The primary data collection and evaluation will take place at 3 time points: the beginning of the project, after 3 months of intervention, and 1 year after the project starts.

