### Statistical Analysis

All analyses will be performed using SPSS. Continuous variables will be presented as mean and SD values. Categorical variables will be expressed as numbers and percentages. Independent samples *t* tests and chi-square tests will be conducted to assess the significance of differences in baseline characteristics or outcomes between the control group and intervention group at 3 time points: before the start of the intervention, 12 weeks after the intervention, and 1 year after the program. Paired *t* tests and McNemar's test will be used to compare the differences in some outcomes before and after the 3-month intervention, as well as before the trial and after the end of the program. A *P* value of less than .05 will be considered statistically significant.

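### Two centres are pooled without a centre term, so a BP difference between them costs precision; adding centre to the model recovers most of that loss

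*Protocol article*

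**What the plan says.** All references are to the Protocol article.

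- **Trial Design and Setting:** "The trial has been conducted at 2 community health centers, both located in Anhui province—1 in Hefei and the other in Bengbu".
- **Randomization, Allocation, and Blinding:** one person used SPSS "to generate 68 random numbers and assigned them to either 1 (experimental group) or 2 (control group) using visual binning". Then "These 68 sets of random numbers were printed separately and sealed in individual envelopes". On their use: "After recruiting a participant, the facilitator opened the envelopes sequentially, and the number found inside each envelope determined the group". No stratum, block or allotment by centre is mentioned.
- **Statistical Analysis:** "Independent samples *t* tests and chi-square tests will be conducted to assess the significance of differences in baseline characteristics or outcomes" between the two groups at each of the three time points. Paired t tests and McNemar's test cover changes over time. None of the named tests has a term for centre.

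The article gives neither the number recruited at each centre nor any BP figure by centre. Results places the data analysis in August 2023 and the 1-year data in September 2023, both still ahead at the time of writing.

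**The concern.** The allocation as described is a single binning of a single set of numbers, which does not balance the arms within each city. The analysis as described then treats the 68 patients as one homogeneous sample. If mean BP differs between Hefei and Bengbu, two things follow. The variation between centres inflates the standard error of the arm difference. And if one centre happens to hold more intervention patients than control patients, part of the centre difference is carried into the estimate from this one trial, with nothing in the analysis to take it out.

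The precision matters because the trial is small and has little power to spare. Centre is known for every patient, so the loss can be avoided at the analysis stage without new data.

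**Working it through.** **Inputs from the article.** N = 68, effect size 0.7 SD, α = .05, β = .2, up to 20% attrition (Sample Size); two centres (Trial Design and Setting).

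**Assumptions, because the article is silent.** 34 patients per arm, 34 per centre, two-sided tests, and a range of centre gaps in mean BP.

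**1. The plan's own figure.** A two-sided t test with d = 0.7 and 80% power needs 33.02 per arm, rounded up to 34, or 68 in total before attrition. With 34 analysed per arm, power is 81.2%. The stated 68 therefore matches a two-sided test with no attrition. A one-sided test needs 26 per arm, and 26/0.8 = 32.5 gives 33 per arm, or 66 in total. That question is separate from this point. It matters here only because the simulations below analyse all 68 patients. With 20% lost, 68 × 0.8 = 54.4, about 27 per arm, power is 71.4%.

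**2. Size of the chance imbalance.** The number X allocated to intervention in one centre is hypergeometric:

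Var(X) = 34 × ½ × ½ × (68 − 34)/(68 − 1) = 8.5 × 34/67 = 4.31, so SD = 2.08.

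A centre gap G shifts the arm difference by G × (2X − 34)/34. At one SD from balance this is G × 2 × 2.08/34 = 0.122 G.

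| Assumed centre gap G | 1 SD shift |
|---|---|
| 3 mm Hg | 0.4 mm Hg |
| 5 mm Hg | 0.6 mm Hg |
| 8 mm Hg | 1.0 mm Hg |

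Unequal centre sizes do not make this worse. At 14 and 54 patients, the SD of the between-arm difference in centre share is 9.9 percentage points, against 12.2 at 34 and 34.

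**3. Validity of the plan as written.** 10,000 trials were simulated for each centre gap (0, 0.5 and 1 within-centre SD), with unstratified 34:34 allocation and the unadjusted t test. Type I error was 4.9% to 5.3%. The mean estimate under no effect was between −0.005 and −0.001 SD. There is no bias and no inflation.

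**4. Precision.** With equal centres and a gap of g within-centre SDs, the variance of a single observation rises from 1 to 1 + g²/4. The SD of the unadjusted estimate is then √[(2/34)(1 + g²/4)], which is 0.243, 0.250 and 0.271 for g = 0, 0.5 and 1. The simulation gave 0.241, 0.251 and 0.273. With centre in the model it gave 0.244, 0.246 and 0.246. Power at an effect of 0.7 SD:

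| Centre gap | Unadjusted t test | Linear model with arm and centre |
|---|---|---|
| 0 | 80.9% | 80.5% |
| 0.5 SD | 77.8% | 79.4% |
| 1 SD | 71.6% | 80.4% |

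The simulation error of each figure is about √(0.8 × 0.2/10,000) = 0.4 percentage points.

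**5. After attrition.** With 27 per arm and the same variance inflation, unadjusted power is 68.8% for a 0.5 SD gap and 61.7% for a 1 SD gap. It is 71.4% if the centre variation is removed, ignoring the small loss from any arm-by-centre imbalance.

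**The case against.** **The plan is only silent.** A journal article condenses the full protocol, which is not shown, and stratification or covariates could be specified there. This stands in part. How the envelopes were shared between two cities is a detail that an article may leave out, and one facilitator covering both centres or a divided sequence would each fit the text. But the article does more than stay silent on method. It describes a single binning of 68 numbers, and it names tests that cannot carry a centre term. If the full protocol says otherwise, the article misdescribes the trial.

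**The stated analysis is valid.** This stands in full. A reader might infer that chance imbalance by centre biases the BP comparison or raises the false-positive rate. It does neither: under unstratified randomisation, the t test's standard error already counts that variation.

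**The harm is easy to exaggerate.** This also stands. A 21:13 split with a 5 mm Hg gap would move the difference by 5 × 8/34 = 1.2 mm Hg, but a split that extreme or worse has a probability of only 9%. The typical shift is half that.

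**Nothing shows that the centres differ.** The article gives one model of BP device, common eligibility criteria, data collectors who are blinded, and an intervention delivered over WeChat from one manual. It does not say who delivers the control group's oral education, so differing local staff cannot be taken as given. The centre gap therefore remains an assumption.

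**Conclusion.** The point holds as a matter of precision, not of validity. As described, allocation is unstratified over two centres and the analysis pools them, so variation in BP between centres stays in the error term and a chance arm-by-centre imbalance goes uncorrected in the realised trial.

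The benefit of adjusting depends on a gap that the article does not give. It is nil if the centres are alike, 1.6 percentage points of power at 0.5 SD (79.4 − 77.8), and 8.8 points at 1 SD (80.4 − 71.6). How many mm Hg these gaps represent depends on the SD of BP, which is not stated. All figures rest on equal arms, equal centres and 68 patients analysed. This is a worthwhile improvement, and the trial's conclusions would not be invalid without it.

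**What to change.** Before the analysis begins, replace the independent-samples t test for BP and the other continuous outcomes at T1 and T2 with a linear model containing arm and centre (Hefei or Bengbu). Report the number in each arm at each centre, so that readers can see the imbalance that actually arose.

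Recruitment has closed, so stratified allocation is no longer open. The simulation shows that adjustment alone recovers most of the loss: at a 1 SD gap, 80.4% power, against 81.4% with stratification as well.

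The change is to the analysis wording only. It uses one degree of freedom, needs no new data, and gains little if the centres turn out to be alike. The sizes above were worked out for a continuous outcome, so no change to the chi-square tests is asked for here.

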### Ethics Approval

This study received approval from the Ethics Committee of Bengbu Medical College (2022-103) in June 2022. Informed written consent forms were obtained from parents with hypertension prior to the start of the study. All the participants agreed to the anonymous use of their data. Upon completing the intervention and data collection at the community health center, the participants were provided with 50 RMB (based on the current exchange rate of US $1=7.29￥, here it is about US $6.86) worth of daily necessities.

### Outcomes

#### Primary Outcomes

BP will be measured using a cardiovascular function monitor (BX-CFTI-100, Institute of Intelligent Machines) at 3 time points: the first baseline assessment phase (T0), the 12-week end point assessments phase (T1), and the end of the 1-year program (T2). The assessment details have been published elsewhere [32].

Exercise adherence (EA), DA, MA, and BPMA indicators were collected once a week through WeChat for the intervention group until T1. The BPMA will also be collected at T0, T1, and T2 for the control group. The exercise adherence indicator was calculated as the ratio of actual exercise time that meets the prescription's recommended intensity to the total time of the prescription-recommended intensity. PAT will be measured as an indicator by questioning subjects in both groups at T0, T1, and T2 about the type, duration (in minutes), and frequency (per week). It will be measured using the minutes or metabolic equivalent per week. The MA indicator will be measured at T0, T1, and T2 for both groups using the Modified Morisky Scale (Chinese version-MMS-8, Certificate Number: 8538-1877-1559-6025-5310) [34-36], which includes 8 simple questions. The rating is “poor medication adherence” for a final total score of <6 points, “moderate medication adherence” for a score of 6-7, and “good medication adherence” for a score of 8. Dietary adherence (DA) will be assessed at T1 and T2 for both groups based on their compliance with the “types of diet” and the “recommended amount of diet” (3 response levels for each question).

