**Methods:**

A 2-arm, parallel-group, and randomized trial design was used. Patients older than 60 years and with hypertension were randomly assigned to either the control group or the experimental group, which received a 12-week intervention. The program, primarily developed based on the Behavior Change Wheel (BCW) theory, offers health education on exercise, diet, BP monitoring, and medicine adherence (MA). It also includes other behavior interventions guided by an intervention manual, incorporating behavior change techniques (BCTs). The primary outcomes encompass BP and adherence indicators, while the secondary outcomes encompass cardiovascular function indicators, body composition indicators, learning performance, satisfaction, and acceptability. The exercise and blood pressure monitoring adherence (BPMA) indicators for the WHBDIP group were assessed weekly via WeChat during the initial 3 months, while other outcome data for both groups will be collected at the baseline assessment phase, 3 months after the intervention, and 1 year after the program.

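### Adherence is a primary outcome, but exercise adherence has no control-arm data and, as written, BP-monitoring adherence is captured differently in the two arms

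*Protocol article*

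**What the plan says.** The Abstract (Methods) states that "The primary outcomes encompass BP and adherence indicators", and the Objective pairs BP control with better adherence. Under Primary Outcomes, "Exercise adherence (EA), DA, MA, and BPMA indicators were collected once a week through WeChat for the intervention group until T1". The next sentence adds that "The BPMA will also be collected at T0, T1, and T2 for the control group". EA is defined as the "ratio of actual exercise time that meets the prescription's recommended intensity to the total time of the prescription-recommended intensity". The same paragraph names both groups for three measures: "PAT will be measured as an indicator by questioning subjects in both groups at T0, T1, and T2"; medication adherence (MA) by the 8-item Morisky scale at T0, T1 and T2; and dietary adherence (DA) by questions at T1 and T2.

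The Abstract draws a similar line: "The exercise and blood pressure monitoring adherence (BPMA) indicators for the WHBDIP group were assessed weekly via WeChat during the initial 3 months", while the other outcomes are said to be collected in both groups at baseline, 3 months and 1 year.

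Intervention Procedure and Monitoring says that the interventionists gathered the exercise, diet, self-measured BP and medication data during the first 3 months. WHBDIP Development says that WeChat also carried the reminders and supervision for BP monitoring and medication. The Discussion accepts that interventionists cannot be blinded. Statistical Analysis plans t tests and chi-square tests of outcomes between the groups at three time points, with no adherence indicator set aside.

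**The concern.** A primary efficacy outcome in a randomised trial needs a value in each arm, obtained in the same way. EA appears to have values in one arm only. BPMA appears to have values in both arms, but from different processes: weekly contact with an unblinded interventionist in one arm, and three assessments in the other.

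Improving adherence is half of the stated objective. For EA, the only available result is a course over time within the intervention arm, which randomisation does not protect and which could be reported as efficacy. For BPMA, a between-arm difference could arise because weekly prompting and recording capture more monitoring than an occasional assessment does, even if behaviour were the same.

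**Working it through.** **Step 1. Compare collection by arm (Abstract and Primary Outcomes).**

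| Indicator | Intervention arm | Control arm | Time points with like-for-like data in both arms |
|---|---|---|---|
| EA | weekly by WeChat to T1 | none stated | 0 of 3 |
| BPMA | weekly by WeChat to T1 | T0, T1, T2 | none on the literal text: T1 by different routes, no T2 value in the intervention arm, T0 unclear |
| MA (8-item scale) | T0, T1, T2 | T0, T1, T2 | 3 of 3 |
| PAT | T0, T1, T2 | T0, T1, T2 | 3 of 3 |
| DA questions | T1, T2 | T1, T2 | 2 of 3 (no baseline) |

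MA and DA also appear in the weekly WeChat sentence, but each has a separate assessment in both groups.

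**Step 2. Is the EA gap only condensed writing?** The same paragraph states control or both-group collection for BPMA, PAT, MA and DA, and states none for EA. The Abstract agrees. The gap is therefore in what the text says, not in detail left out for space. A control value was conceivable, because controls received "oral health education about printed exercise prescriptions", but none is described.

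**Step 3. Can PAT stand in for EA?** EA counts only exercise time at the prescribed intensity, relative to the prescribed time. PAT asks for type, duration and weekly frequency. Intensity is not among the listed items, so the EA numerator cannot be shown to be obtainable from PAT.

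**Step 4. Group size.** Randomization describes 68 random numbers split into two groups. The ratio is not given, so 1:1 is assumed: 68 / 2 = 34 per arm. As a check on the plan's figure, effect size 0.7, two-sided α = 0.05 and power 0.80 give 34 per arm by the t test, a total of 68 before any attrition allowance. With one-sided α, 26 per arm gives 52, and 52 / 0.8 = 65. That question is separate; only the 34 is used here. With 20% attrition, 34 × 0.8 ≈ 27 per arm.

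**Step 5. Illustration for BPMA.** The documents give no figure for a capture difference, so a range is assumed. Suppose that there is no true effect and that capture alone shifts the arm means by b SD. The two-sided 5% t test then follows a noncentral t distribution with λ = b × √(n/2) and 2n − 2 degrees of freedom.

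- n = 34: √17 = 4.123, df = 66, critical value 1.997.
  - b = 0.2: λ = 0.825, rejection rate 12.8%
  - b = 0.3: λ = 1.237, rejection rate 23.0%
  - b = 0.5: λ = 2.062, rejection rate 52.9%
- n = 27: √13.5 = 3.674, df = 52, critical value 2.007. The same shifts give 11.1%, 19.1% and 43.8%.

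The nominal rate is 5%.

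**The case against.** **No between-group EA test is named.** Statistical Analysis speaks of outcomes in general, and Results expects adherence indicators to change during the 3 months, which fits a within-arm description. This softens the point but does not remove it. EA sits under Primary Outcomes, is not marked as descriptive, and is not exempted from the group comparisons.

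**The trial can still assess adherence.** This stands. MA, PAT and DA are collected in both groups, and BP, which drives the sample size, is measured by the same device at all three time points. A reader might infer that the whole adherence objective fails; the documents do not support that.

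**BPMA may share a schedule.** The word *also* in the control-arm sentence can be read as adding controls to a T0/T1/T2 collection in both arms. Data Collection and Management refers to health-related data at those time points without limiting it to one arm, and the flowchart is not shown. This stands as a real ambiguity. Against it, the sentence names only the control group where neighbouring sentences name both, and the Abstract describes intervention-arm BPMA as weekly WeChat data. A reader might infer that BPMA is certainly biased; the text supports only a risk, together with a need to reconcile it.

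**Data collectors were blinded.** The Randomization section says so for before and after the trial. That may protect assessments at the time points. It does not reach records gathered by interventionists during the programme.

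**Cash rewards.** A reader might infer that money was paid for uploading BP records. Table 2 lists a WeChat cash reward but does not say what earns it, so nothing here rests on it.

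**Conclusion.** The point holds in two parts of different strength.

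- **EA: firm, with no assumption needed.** None of the three time points has data in both arms, so no randomised effect on EA can be estimated as the article is written.
- **BPMA: conditional on the literal reading.** On that reading there is no T2 comparison, and a T1 comparison confounds effect with data capture. The direction would plausibly favour the intervention, but the size cannot be derived from the documents. The rates of about 13%, 23% and 53% rest on assumed shifts of 0.2, 0.3 and 0.5 SD, no true effect, equal allocation and 34 per arm. They show sensitivity and do not estimate the actual bias.

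MA, PAT and DA remain usable for between-arm comparison, with DA lacking a baseline.

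**What to change.** 1. Reclassify the weekly WeChat EA, DA, MA and BPMA data as intervention-arm process measures, reported descriptively with no efficacy P value.
2. Base between-arm adherence comparisons on measures taken the same way in both arms: the 8-item medication scale and PAT at T0, T1 and T2, and the dietary questions at T1 and T2 only.
3. Reconcile the BPMA wording in the Abstract and Primary Outcomes, stating for each arm the time points, the question and the recall window.
4. Ask BPMA with the same question and recall window in both arms at T2. Report T1 BPMA descriptively unless both arms were asked the same question then.
5. Do not derive a comparative EA from PAT unless exercise intensity was recorded in both arms.

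The cost is protocol and analysis-plan wording plus one question at T2. On the article's timeline, T1 collection ended in January 2023, so it cannot be repaired if the question differed, while T2 collection was still to come in September 2023. The downside is that EA loses primary-outcome status.
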